**Introduction**

Acute myocardial infarction (AMI) is a serious killer threatening human life and health, with high mortality and morbidity worldwide. At present, the treatment of acute myocardial infarction mainly includes drug therapy, percutaneous coronary intervention (PCI) and coronary artery bypass grafting (CABG), etc. Although the reperfusion and the best drug therapy technologies are mature, the reperfusion process may cause further injury, which is called myocardial ischemia-reperfusion injury (IRI)^1,2^, can cause a series of pathophysiological changes such as myocardial stunning, energy metabolism disorder and microvascular dysfunction^3^, and aggravate irreversible damage such as glycogen depletion, nuclear chromatin margination, mitochondrial swelling, sarcolemma rupture^4^, however, there is no specific drug in the world to solve this problem.

Extracorporeal cardiac shock wave therapy (ECSW) is a cutting-edge technology developed in the world for more than 20 years. In 2004, ECSW was approved by European CE certification. In the early stage, the efficacy, safety and mechanism of action were discussed in Germany, Japan, Switzerland, Italy and other countries. It is mainly used to treat refractory angina pectoris of coronary heart disease. The mechanism of ECSW is mainly due to the small attenuation, small shear stress, and strong penetration of shock wave in human tissues, resulting in shear stress and cavitation effect in the focal region of the shock wave, triggering microbubbles to form/burst repeatedly within the tissue/cell microenvironment, producing a variety of physical and biological effects^5^ and these physical mechanisms trigger a range of biological effects, for example, it can promote the expression of many kinds of cytokines and angiogenic factors, activate related signal transduction pathways, inhibit apoptosis and oxidative stress, and finally increase the number of new blood vessels in the therapeutic area, improve the ischemic state.

The present results suggest that ECSW can effectively treat refractory angina pectoris, significantly improve the clinical symptoms and quality of life, and improve exercise tolerance in patients with heart failure, providing a new treatment option for patients with severe advanced coronary artery disease^5^. However, clinical studies of ECSW during this period have been relatively few, given that the early phase of acute myocardial infarction is characterized by a high incidence of cardiovascular events. In 2018, Japanese scholars reported that 17 patients with acute myocardial infarction underwent three ECSWS within 48-72h after direct PCI, and echocardiography, cardiac magnetic resonance and left ventricular angiography were used to evaluate left ventricular size and function, and 25 patients were matched as the control group. The 6-month follow-up indicated that LVEF in the ECSW group was significantly improved and the left ventricular diameter showed a decreasing trend, but the difference was not statistically significant^6^. However, due to the small sample size and short follow-up period, whether ECSW can help improve ventricular remodeling in patients with acute myocardial infarction remains to be further studied and explored. We hypothesized that in vitro cardiac shock therapy was effective in reducing the clinical end point in patients with acute ST-segment elevation myocardial infarction reperfusion.

Therefore, we designed this prospective randomized controlled clinical trial to evaluate the clinical efficacy and safety of in vitro cardiac shock therapy for patients with myocardial ischemia-reperfusion injury, with a view to providing a novel therapy for patients with myocardial ischemia-reperfusion injury.

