**Methodology**

**Study aim and objectives**

This study is order to provide a new therapeutic method for patients with myocardial ischemia-reperfusion injury and reveal the possible mechanism of ECSW for ischemia-reperfusion injury.

The objectives of the study as follows:

**I.** The primary endpoint of this study is 2-year all-cause death, rehospitalization due to cardiovascular disease, major adverse cardiovascular and cerebrovascular events, including cardiac death, myocardial infarction, heart failure, arrhythmia, emergency coronary revascularization, and stroke;

**II.**Secondary endpoints are improvement in angina, quality of life, cardiac structure and function, coronary microcirculation, and expression level of endothelial progenitor cell-derived miR-140-3p.

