The experimental group meeting the inclusion and exclusion criteria will be treated by the external cardiac shock therapy instrument in accordance with standard operating procedures, specifically to determine the treatment target myocardium: according to the conventional left ventricular myocardium will be divided into 17 segments, through load ultrasound or load nuclide myocardial perfusion imaging, combined with ECG, coronary angiography and other results, to determine the therapeutic bullsey-eye muscle segments. Vital signs monitoring: During treatment, patients will be required to lie in a quiet position, and 12-lead combined electrocardiogram (ECG) will be recorded, connected to ECG, blood pressure and oxygen saturation monitoring. Setting the height of the water sac: Adjust the height of the water sac (positioning) according to the location of the target myocardium before positioning, and then move the ultrasonic probe down and slightly protruding from the surface of the water sac to achieve clear positioning. After positioning, it is appropriate to increase the height of the water sac until the patient's chest wall is lightly touched but not compressed, in order to reduce the energy attenuation in the process of seismic wave conduction. Airborne ultrasonic detection of bull's eye muscle segments: When the probe moves down and touches the chest wall, the left ventricular long axis image will be displayed first, and then the ultrasonic adjustment button will be rotated clockwise to display the left ventricular short axis, four chambers and two chambers of the left heart section in turn. When more than two sections lock the same segment together, the positioning will be regarded as successful. Energy control: Raise the probe after positioning so as not to interfere with shock wave release. Then press the shock wave releaser, starting from a small energy level of 0.8 (equivalent to 0.024 mJ/mm2). The successful release is marked by the occurrence of "Da, da" sound consistent with the patient's heart rate. Every 200 points is one frequency cycle. If there is no special, the energy level can be gradually adjusted to level 3 (0.09 mJ/mm2); Fine-tuning of treatment points in the target area: under normal circumstances, we will line a combination of 9 points between 1 ~ 0 ~ -1 or 2 ~ 0 ~ -2 for each area, and issue 200 pulses at each point, giving a total of 1800 pulses (9×200). Monitoring during treatment: ask patients about their symptoms and observe their vital signs and electrocardiogram. In case of discomfort or changes in electrocardiogram, lower the energy level first and continue to observe, treat as appropriate, record and analyze the causes in detail.

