
**Data collection and follow-up**

All necessary data will be collected and recorded in electronic case report forms for this study, which will be mainly obtained from medical records(such as electronic or paper medical records), local laboratory testing records and investigator’s evaluation on patients. Relevant baseline data will be collected at the time of enrollment in patients with acute ST-segment elevation myocardial infarction reperfusion, mainly including:demography(age, gender, race), medical history, signs, treatment, biochemical values(mainly including serum electrolyte value, serum AST, serum ALT, serum creatinine, serum BUN, serum CK-mb, cTNI, BNP and HsCRP), imaging examination indicators(Echocardiography will be used to measure left ventricular ejection fraction (LVEF), left ventricular end diastolic diameter(LVEDD), global longitudinal strain, myocardial stress changes in each segment and synchrony of myocardial motion, left ventricular contrast echocardiography will assess coronary microcirculation), relevant scale scores(mainly will include 6-minute walk test, Canada Cardiovascular Society (CCS) angina classification, Seattle angina scale (SAQ) score, quality of life scale (SF-8)) (Appendix D) and expression level of miR-140-3p in endothelial progenitor cell (EPCs)-derived exosomes in peripheral blood;Biochemical values, imaging parameters, scores of relevant scales, expression level of miR-140-3p in endothelial progenitor cell (EPCs)-derived exosomes and major adverse cardiovascular events (which will include all-cause death, readmission due to cardiovascular disease, cardiac death, myocardial infarction, heart failure, arrhythmia, emergency coronary revascularization and stroke) will be collected in the test group and control group at 1, 4, 6, 12 and 24 months.

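### Safety is a stated purpose, but no safety endpoint is designated, and harms outside the cardiovascular composite, laboratory values and scales are not collected comparably in the two arms

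*Protocol*

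**What the plan says.** The Introduction ends by saying that the trial was designed "to evaluate the clinical efficacy and safety of in vitro cardiac shock therapy for patients with myocardial ischemia-reperfusion injury".

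Study aim and objectives then sets the endpoints. The first is introduced as "The primary endpoint of this study is 2-year all-cause death, rehospitalization due to cardiovascular disease, major adverse cardiovascular and cerebrovascular events", followed by the component events. The rest are: "Secondary endpoints are improvement in angina, quality of life, cardiac structure and function, coronary microcirculation, and expression level of endothelial progenitor cell-derived miR-140-3p". None is designated as a safety endpoint. Research hypothesis and Study design do not mention safety.

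Data collection and follow-up lists a baseline laboratory panel that includes "serum electrolyte value, serum AST, serum ALT, serum creatinine, serum BUN, serum CK-mb, cTNI, BNP and HsCRP". For follow-up it lists biochemical values, imaging parameters, scale scores and miR-140-3p expression. It also has an event item, "major adverse cardiovascular events (which will include all-cause death, readmission due to cardiovascular disease, cardiac death, myocardial infarction, heart failure, arrhythmia, emergency coronary revascularization and", which closes with stroke. All of these "will be collected in the test group and control group at 1, 4, 6, 12 and 24 months".

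Study intervention describes what is watched while shock waves are delivered: "Monitoring during treatment: ask patients about their symptoms and observe their vital signs and electrocardiogram". If discomfort or an ECG change occurs, staff are, among other things, to "treat as appropriate, record and analyze the causes in detail".

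**The concern.** A trial that sets out to evaluate safety needs two things in its protocol: a statement of which outcomes answer the safety question, and a collection scheme that gathers those outcomes in the same way in both arms. The first is absent. The second is only partly present, because the events collected in both arms are those of the primary endpoint.

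A non-fatal harm of another kind has no place in the follow-up list for either arm. Examples are a skin or chest-wall reaction, a non-cardiovascular illness, or a hospital stay for a non-cardiovascular reason. Treated patients have an open-ended record during sessions; controls have no counterpart.

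The protocol itself says that clinical studies of this treatment early after infarction are few, and it cites one with 17 treated patients and three sessions each. This trial plans nine sessions per patient in up to 51 patients, so its harm data would be informative. They would be lost or uncontrolled if the plan were followed as written.

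**Working it through.** **1. What is collected, by arm**

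| Kind of harm | Shock-wave arm | Control arm | Comparable between arms? |
|---|---|---|---|
| Death; cardiovascular readmission; infarction; heart failure; arrhythmia; emergency revascularization; stroke | 1, 4, 6, 12, 24 months | same | Yes |
| Laboratory abnormality | same five visits | same | Yes, if the follow-up panel is the baseline panel |
| Pain, limitation, angina (SF-8, Seattle scale) | same five visits | same | As scale scores only; they do not record events or causes |
| Symptoms or ECG change during a session | each session, open-ended | no sessions | No |
| Other non-fatal harms, including local and device-related ones, outside sessions | no item | no item | No |

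The word in Data collection and follow-up that leaves a list open (mainly) qualifies the baseline items. The follow-up items are simply named.

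**2. The number of patients**

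Sample size estimation gives a control LVEF of 58.0 with SD 11.7, a gain of 8.1, alpha 0.05 and power 90%. Reading 8.1 as points and the test as two-sided:

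2 × (1.960 + 1.282)² × 11.7² / 8.1² = 43.8, so 44 per arm, as stated.

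The allowance for loss gives 44 × 1.15 = 50.6, so 51 per arm, also as stated. This figure is not in dispute. It is the input for the next two steps.

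**3. Precision for harms collected in both arms**

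The protocol gives no event rates, so these are assumptions. With the same true rate p in each arm, the 95% half-width for the risk difference is 1.96 × √(2p(1 − p)/51):

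- p = 5%: 1.96 × √(0.095/51) = 8.5 percentage points
- p = 10%: 1.96 × √(0.18/51) = 11.6 points
- p = 20%: 1.96 × √(0.32/51) = 15.5 points

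Power to detect an excess (two-sided 5%, 51 per arm) is Φ[(d − 1.96 × SE₀)/SE₁], where SE₀ uses the pooled rate and SE₁ the separate rates. For 5% against 20%:

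- SE₀ = √(2 × 0.125 × 0.875/51) = 0.0655
- SE₁ = √((0.0475 + 0.16)/51) = 0.0638
- (0.15 − 1.96 × 0.0655)/0.0638 = 0.34, so power is about 63%

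In the same way, power is about 29% for 10% against 20% and about 16% for 5% against 10%.

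**4. Precision for a harm never seen in one arm**

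The one-sided 95% upper limit for 0 of 51 is 1 − 0.05^(1/51) = 5.7%. With 44 patients it is 6.6%. These limits follow from the sample size, not from the gap in collection.

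**5. Harms not collected**

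At most 51 × 9 = 459 sessions carry open-ended recording, all in one arm. That shows where the recording sits; it does not measure a bias. For the last two rows of the table there is no control-arm figure, so no risk difference can be formed.

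**The case against.** The strongest reply is that the trial does collect safety information in both arms. For a cardiac treatment begun days after PCI, death, arrhythmia, infarction, heart failure and stroke are central safety outcomes, and all are recorded in controls at five visits. All-cause death includes non-cardiovascular death. Liver, renal and cardiac markers are in the baseline panel, and biochemical values are repeated. The SF-8 asks about pain. All of this stands. A reader might infer that nothing adverse is recorded in controls, or that the safety question cannot be answered at all. The follow-up list contradicts both readings.

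A reader might also set in-session counts in treated patients against zero in controls and predict a false signal. The Data analysis section plans no such comparison, and controls who were never observed are not controls with zero events.

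It can further be said that safety appears as a purpose only in one clause of the Introduction. That is correct, and it makes part of the point an inconsistency between that clause and the sections that set the objectives. It does not remove the gap in collection.

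Finally, a statistical analysis plan may define safety tables. It may well do so, for instance by using the composite and laboratory values as safety data. It cannot tabulate adverse events that the protocol does not ask anyone to record.

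**Conclusion.** The point holds in a limited form. Safety is named as a purpose and no endpoint is designated for it. Cardiovascular harms and laboratory values can be compared between arms, with low precision at 51 per arm: roughly ±8.5 to ±15.5 percentage points for assumed rates of 5% to 20%. Non-fatal harms outside the composite and laboratory values, including local and device-related ones, cannot be compared beyond what the scale scores reflect.

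This rests on taking the follow-up list as complete and on the follow-up laboratory panel being the baseline one. The flow diagram in Appendix C and the case report form could not be checked. If either already provides for adverse events in both arms, the protocol text still needs to say so, but the data would not be lost.

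**What to change.** - **Study aim and objectives:** add a safety objective, namely the proportion of patients with at least one adverse event and the proportion with at least one serious adverse event. State that the composite's events and the laboratory values will also be reported as safety data.
- **Data collection and follow-up:** add adverse events with onset date, asked with the same questions in both arms at the existing 1, 4, 6, 12 and 24 month contacts.
- **Data analysis:** report risk differences between arms with 95% confidence intervals. Describe in-session findings for the shock-wave arm separately and keep them out of the between-arm comparison. Otherwise ECG changes that only session monitoring brings to light could be set against an arm without such monitoring.

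The cost is a short amendment, one case-report-form page per visit and one table. No new visit, procedure or patient is needed.

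Two weaknesses remain and should be stated as limitations. Recall reaches 12 months between the last two visits; over the three-month treatment course it is at most three months, from the 1-month to the 4-month visit. Ascertainment also stays unequal, because treated patients have nine extra contacts and there is no sham. Deleting safety from the Introduction would remove the inconsistency but would collect no harm data, so it is the weaker option.

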**Methodology**

**Study aim and objectives**

This study is order to provide a new therapeutic method for patients with myocardial ischemia-reperfusion injury and reveal the possible mechanism of ECSW for ischemia-reperfusion injury.

The objectives of the study as follows:

**I.** The primary endpoint of this study is 2-year all-cause death, rehospitalization due to cardiovascular disease, major adverse cardiovascular and cerebrovascular events, including cardiac death, myocardial infarction, heart failure, arrhythmia, emergency coronary revascularization, and stroke;

**II.**Secondary endpoints are improvement in angina, quality of life, cardiac structure and function, coronary microcirculation, and expression level of endothelial progenitor cell-derived miR-140-3p.

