**Study setting and subjects**

The study protocol and implementation will have complied with the principles of Declaration of Helsinki^7^. Firstly, The study will be approved by the Ethics Review Committee of the First Affiliated Hospital of Kunming Medical University. Permission will also be obtained from the Director of the First Affiliated Hospital of Kunming Medical University. Secondly, the purpose of the study, the data collection procedures, the potential risk and benefits, the maintenance of confidentiality, and the voluntary basis of participation will be clearly explained to the participants. Participants will be informed that they have the choice to withdraw from the study at any time if they choose to do without penalty or negative consequence of current health services.

Thirdly, the informed consent will be provided in written and oral form when the research personnel approaches the potential participants. The detailed information and explanation of the nature of the study, the right of participants to withdraw from the study at any time, the anonymity and confidentiality of the participants, contact details of the researcher which participants may contact to obtain further information if they need will be included in the subject information sheet. Fourthly, to maintain the anonymity of the participants, they will be asked not to write their name in the questionnaire, however, the code number will be provided by the researcher. All data will be kept by the principal investigator in a password-protected computer and a locked cabinet to ensure the confidentiality of participants. The participants will be informed that all personal data will only be accessed by the principal investigator and all the collected data will be destroyed five years after the study completion.

This study will be conducted in the First Affiliated Hospital of Kunming Medical University. The study site is a 4,000-bed hospital serving more than 40 million people in Yunnan Province and neighboring regions. Most acute myocardial infarction patients in Yunnan province will receive treatment at the hospital. Study participants will be recruited from study hospital wards. The intervention will be performed at the hospital's cardiology outpatient clinic. The hospital provides multidisciplinary services, including cardiologists, doctors, nurses and other health care workers. The flow chart for the main study is shown in Appendix C.

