**Inclusion and exclusion criteria**

The eligibilities of participants are; ≥18 years old; Acute ST-segment elevation myocardial infarction was diagnosed for the first time, and coronary angiography indicated moderate to severe coronary artery stenosis. PCI was performed within 12 hours of the onset of the disease according to the current guidelines, and the postoperative hemodynamics were stable; CCS angina pectoris grade Ⅱ and above, NYHA cardiac function grade I-Ⅲ; Imaging examination [stress echocardiography and/or stress myocardial perfusion imaging] suggested objective evidence of reversible myocardial ischemia; Voluntary participation, able to cooperate with treatment and follow-up, signed informed consent.

Exclusion criteria will include: unprotected severe left main disease; Left ventricular systolic function was impaired and hemodynamic instability was observed. Poor sound window in ultrasound examination due to chronic obstructive pulmonary disease, bullae, pseudobreast implantation or other reasons; Combined with breast malignancy; Pregnancy; Treatment area skin ulceration or infection; NYHA cardiac function grade Ⅳ; Acute myocarditis, pericarditis, moderate or large pericardial effusion, infective endocarditis, deep vein thrombosis, intracardiac thrombus; Severe aortic stenosis, aortic aneurysm, thoracic aortic dissection, thoracic aortic aneurysm, heart transplantation, metal heart valve replacement, pulmonary embolism; Patients undergoing thrombolysis and surgical bypass; Patients with a history of mental illness, poor compliance and inability to cooperate.

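### The primary endpoint restricts revascularization to emergencies, but its unrestricted cardiovascular rehospitalization component still counts elective procedure admissions as events

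*Protocol*

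**What the plan says.** Under Study aim and objectives, the protocol's primary endpoint at 2 years is all-cause death together with "rehospitalization due to cardiovascular disease, major adverse cardiovascular and cerebrovascular events, including cardiac death, myocardial infarction, heart failure, arrhythmia, emergency coronary revascularization, and stroke". Rehospitalization has no qualifier; revascularization has one.

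Data collection and follow-up repeats the pair in the list of events to be recorded at 1, 4, 6, 12 and 24 months: "readmission due to cardiovascular disease, cardiac death, myocardial infarction, heart failure, arrhythmia, emergency coronary revascularization and stroke". The wording is therefore not a slip in one place. Nothing in the protocol excludes elective, scheduled or staged admissions, and no event definition or adjudication step is described that would do so.

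Three inclusion criteria bear on how likely such admissions are: "coronary angiography indicated moderate to severe coronary artery stenosis", "CCS angina pectoris grade Ⅱ and above", and stress imaging that "suggested objective evidence of reversible myocardial ischemia". Under Randomization, controls go to a blank group and no sham procedure is described.

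**The concern.** Restricting revascularization to emergencies makes a difference only if some non-emergency procedures do not count. A patient brought back for an elective coronary procedure has, however, been rehospitalized for cardiovascular disease. One component of the primary endpoint leaves the procedure out and another brings it in.

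Two things are at stake. First, a planned admission is not in itself a treatment failure. If such admissions are equally common in both arms, they add events unrelated to treatment and pull the risk ratio toward 1. Second, elective admission is a decision made by patients and clinicians. Patients know whether they received shock wave therapy, and their clinicians can learn it. If that knowledge changes the threshold for elective admission, the arms can differ without any true effect.

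**Working it through.** **1. The wording, applied to one case.** Take a patient electively admitted for coronary revascularization in month 8.
- Revascularization component: not an emergency, so no event.
- Rehospitalization component: a cardiovascular admission with no exclusion, so an event.
- Result: a primary event.

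The same holds for any elective procedure that needs a new admission. For those procedures the emergency limit changes nothing.

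**2. Does study treatment itself create such admissions?** No. Study setting and subjects states: "The intervention will be performed at the hospital's cardiology outpatient clinic". Treatment sessions are not described as admissions, so the problem concerns ordinary elective care.

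**3. The plan's own figures.** The protocol gives no event rate for the primary endpoint. Its sample size rests on LVEF and reproduces: 2 × (11.7 × (1.960 + 1.282) / 8.1)² = 43.8, rounded up to 44 per arm, and 44 × 1.15 = 50.6, rounded up to 51. It does not bear on the wording; 51 per arm is used below only as the size of an arm.

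**4. Dilution, on assumed figures.** Let p be the 2-year risk of an event other than a planned admission, and q the risk of a planned cardiovascular admission, independent of p and equal in both arms. The observed risk is 1 − (1 − p)(1 − q). Assume p = 30% in control and 20% with shock wave, a ratio of 0.67.

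| q | Control | Shock wave | Ratio | Added events per arm of 51 (control; shock wave) |
|---|---|---|---|---|
| 0 | 30% | 20% | 0.67 | 0; 0 |
| 10% | 1 − 0.70 × 0.90 = 37% | 1 − 0.80 × 0.90 = 28% | 0.76 | 51 × 0.07 = 3.6; 51 × 0.08 = 4.1 |
| 25% | 1 − 0.70 × 0.75 = 47.5% | 1 − 0.80 × 0.75 = 40% | 0.84 | 51 × 0.175 = 8.9; 51 × 0.20 = 10.2 |

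The last column counts only patients who become events solely through a planned admission.

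**5. Sensitivity to the assumptions.** Power is the normal approximation for two proportions, two-sided 5%, 51 per arm: Φ{(|p₁ − p₂| − 1.96 √[2p̄(1 − p̄)/51]) / √[(p₁(1 − p₁) + p₂(1 − p₂))/51]}.
- With p = 30% versus 18% (ratio 0.60), power is 29% at q = 0.
- At q = 20% the rates are 44.0% versus 34.4% (ratio 0.78) and power is 17%.
- Over control risks of 20–40% and true ratios of 0.5–0.7, q = 20% moves the ratio to about 0.69–0.87 and power from 12–60% to 7–37%.

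**6. Bias, on assumed figures.** Set p = 30% in both arms, so there is no true effect. Planned admissions of 25% in control and 15% with shock wave give 1 − 0.70 × 0.75 = 47.5% versus 1 − 0.70 × 0.85 = 40.5%, a false benefit of 7 points. Exchanging the two planned rates gives a false harm of the same size. The documents do not say which is more likely.

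**The case against.** The strongest reply is that no contradiction is stated. Rehospitalization and emergency revascularization are separate items, and the same sentence sets all-cause death beside cardiac death, so a broad item next to a narrow one is simply how it is written. All cardiovascular rehospitalization is a usable endpoint, and a statistical analysis plan or event form that is not shown might separate planned from unplanned admissions. What stands is that the protocol does not state the authors' intent. The effect of the wording does not depend on intent, though, and the definition of the primary endpoint belongs in the protocol.

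One could also point to the Randomization section, which withholds assignment details from the investigator and separates treatment practitioners from evaluators. That does not help here: once an elective admission has happened it meets the definition, whoever scores it.

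Several stronger readings are tempting but unsupported:
- **That most participants await staged PCI.** Staged PCI appears nowhere. The protocol does not say when angina grade and stress imaging are assessed relative to the index PCI, so residual ischaemia after it cannot be assumed for every patient.
- **That planned admissions hide later deaths, infarctions or strokes.** This requires a time-to-first-event analysis of the combined endpoint. Data analysis names Kaplan-Meier, log-rank and Cox methods for time-to-event variables in general and does not say this.
- **That the trial will show a false benefit.** The direction is unknown.
- **That heart failure present at entry would be scored as an event.** NYHA I–III patients are eligible, but heart failure is collected as an adverse event at follow-up, which ordinarily means an occurrence after enrolment.

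**Conclusion.** The point holds as one about endpoint wording. As the protocol stands, elective cardiovascular admissions are primary events, and the emergency limit on revascularization has no effect for procedures that need a new admission. Such admissions are plausible over 2 years given the required stenosis, angina and reversible ischaemia, but the documents give no rate.

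Confidence is high on the text and low on the size. The illustrated shift of a ratio from 0.67 to 0.76 or 0.84 rests on an assumed 30% versus 20% true risk, equal planned admissions of 10% or 25%, and independence of the two. The possible bias rests on the blank control without a described sham and on the discretionary nature of elective admission; its sign and size cannot be derived from the documents.

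**What to change.** In both Study aim and objectives and Data collection and follow-up, change the component to unplanned rehospitalization due to cardiovascular disease. Record on the event form whether each cardiovascular admission was planned or unplanned. Report planned admissions and planned revascularization separately by arm, so that a difference in elective care remains visible.

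The cost is a short protocol amendment and one extra field. Patient care is unchanged. There will be fewer primary events, by a number that depends on the unknown planned-admission rate; in the illustration it is about 4 per arm at 10%, and about 9 in control and 10 with shock wave at 25%. The change reduces bias from known allocation but does not remove it, because unplanned admissions and other components that depend on judgement can also be influenced.
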